# A protocol for a multidisciplinary early intervention during chemotherapy to improve dietary management behavior in breast cancer patients: a two-arm, single-center randomized controlled trial

**DOI:** 10.1186/s12885-024-12623-w

**Published:** 2024-07-18

**Keywords:** Breast cancer, Chemotherapy, Diet, Health management behavior, Nutrition, Quality of life

## Abstract

**Background:**

Adverse reactions are prone to occur in the early stage of chemotherapy and can negatively affect the dietary intake and nutritional status of breast cancer (BC) patients. Consequently, they need to participate in health self-management and lifestyle promotion programs. Early multidisciplinary interventions aim to enhance dietary management behavior and quality of life in chemotherapy-treated BC patients.

**Methods:**

This single-blinded, single-center, randomized controlled trial will include 88 females who have not yet started the early or middle stage of the chemotherapy cycle. A random number table will be used randomly assign females to the intervention group or usual group at a 1:1 ratio. The intervention elements are based on the theoretical guidance of the Integrated Theory of Health Behavior Change (ITHBC). A multidisciplinary team (MDT) comprising oncologists, dietitians, nurses, traditional Chinese medicine (TCM) practitioners, and psychologists will provide the intervention. Intervention sessions will be conducted once a week for 8 weeks, beginning in the early or middle stage of the chemotherapy cycle and continuing through admission and a home-based interval chemotherapy period. The intervention includes face-to-face discussions, online meetings, WeChat messaging, and telephone calls. The themes target adverse reactions, dietary information and habits, self-care self-efficacy, treatment self-regulation, dietary supplement and TCM use, social support, weight management, and outcome expectations. The primary outcome is dietary management behavior measured by the Dietary Management Behavior Questionnaire (DMBQ). Secondary outcomes are self-care self-efficacy assessed by the Strategies Used by People to Promote Health (SUPPH); quality of life measured by the Functional Assessment of Cancer Therapy-Breast (FACT-B); and body mass index (BMI) measured by an electronic meter. All participants will be assessed at baseline and immediately, 1 month, 3 months, 6 months, and 12 months after the intervention.

**Discussion:**

Early dietary intervention is needed, as diet is one of the most common health self-management behaviors influenced by chemotherapy. Early multidisciplinary interventions may provide a foundation for dietary self-management and improve nutritional status in the survival period.

**Trial registration:**

This intervention protocol was registered with the Chinese Clinical Trials Registry (ChiCTR2300076503, October 10, 2023).

**Supplementary Information:**

The online version contains supplementary material available at 10.1186/s12885-024-12623-w.

## Background

According to the latest global cancer epidemiological data released by the World Health Organization [1], there were approximately 2.3 million new cases of breast cancer (BC) in 2020, accounting for 11.7% of all new cancer cases worldwide (excluding basal cell carcinoma). Furthermore, there were approximately 400,000 new cases of BC among Chinese women in 2020, and this number is expected to increase further [2]. Although the incidence of BC is high, several studies [2, 3] have confirmed that the 5-year relative survival rate can reach 40.5% or more, and the proportion of survivors is also increasing steadily. This is primarily attributed to improvements in diagnosis and treatment.

At present, chemotherapy is one of the most common and essential therapies for treating BC. The vast majority of BC patients receive chemotherapy after diagnosis. However, a series of side effects caused by chemotherapy, such as nausea, vomiting, loss of appetite, taste disorders, and gastrointestinal symptoms, can seriously affect the dietary intake and nutritional status of BC patients. This further exacerbates weight gain and muscle strength loss and has a profound negative impact on the quality of life and psychological state of BC survivors [4]. Possible reasons include the following: first, drug-related toxicity leads to muscle depletion due to decreased protein anabolism and proatrophic mechanisms, resulting in decreased skeletal muscle mass and increased fat mass; second, chemotherapy can cause ovarian failure, which affects hormone levels and is also associated with subsequent weight gain; third, chemotherapy-related fatigue can reduce daily physical activity and energy expenditure at rest, resulting in weight gain; and finally, chemotherapy can lead to changes in taste and smell and can cause changes in eating habits, which can affect weight [5]. Diet is one of the most important lifestyle factors and is considered a self-management health behavior involving physiological, psychological, environmental, social, and other factors [6]. Some researchers [6, 7] have proposed early nutritional interventions at the beginning or in the middle of chemotherapy, but specific evidence about BC patients needs to be supplemented. Therefore, BC patients’ dietary management behavior (DMB) during chemotherapy should be considered.

There are few existing studies about dietary management interventions for cancer patients during chemotherapy, and the available studies lack specificity. First, regarding the intervention population, most studies [8–10] have focused on BC survivors who have completed all adjuvant therapy. However, many females report the most severe side effects during chemotherapy. They do not know how to cope with these side effects and receive little support during treatment [11–13]. Thus, early dietary intervention is needed. Regarding intervention content, most cancer patients are thought to be provided with professional nutritional supplements [14, 15]. The nutritional status of most cancer patients does not reach severe pathological malnutrition. Instead, they can feed themselves orally and desire increased knowledge about nutrition and dietary precautions. Implementing DMB interventions is highly beneficial. These interventions can stimulate patients’ sense of autonomy, cultivate their nutritional management ability, provide a basis for the implementation of home-based rehabilitation plans after chemotherapy, and ultimately improve their life expectancy and quality of life [5].

Additionally, diet and nutrition promotion are usually framed as the work of oncologists and dietitians. Nevertheless, diet is an integral part of one’s lifestyle and a health management behavior that includes physiological, psychological, environmental, societal, and cultural elements [16, 17]. In China, cancer patients also desire advice on food therapy or integrative medicine from traditional Chinese medicine (TCM) practitioners [18, 19]. A multidisciplinary team (MDT) comprising oncologists, dietitians, clinical nurses, TCM practitioners, and psychologists may be suitable for providing diet management interventions.

Many previous interventions were designed without theoretical guidance, and only a few intervention studies considered social cognition theory [9, 10, 20, 21], cognitive behavior theory [22], or World or American Cancer Guidelines [8, 23]. Most studies have focused on weight management, nutrient intake, and exercise among BC survivors. Chemotherapy side effects can disrupt patients’ regular diets and require self-management behaviors to transition to a healthy diet. By integrating the core concepts of a variety of commonly used theoretical models that affect health behavior change (such as self-regulation theory, health behavior change theory, and social facilitation theory) and through empirical research, a patient-centered and dynamic middle domain theory model called the ‘Integrated Theory of Health Behavior Change (ITHBC) was developed. The ITHBC states that ‘change’ is a dynamic and circular process, emphasizing that establishing behaviors requires the combined effects of multiple aspects such as improving patient cognition, enhancing self-management skills, and creating a supportive environment [24]. According to this theory, the factors related to health behavior change include knowledge and beliefs, self-regulation, and social support; the resulting health behavior is the proximal outcome, and the health status is the distal outcome. Based on the ITHBC, one study [25] used corresponding variables to evaluate the factors influencing weight management in overweight postpartum women. The results showed that knowledge and beliefs about self-efficacy, outcome expectations, self-regulation, and social support could affect weight management behavior. However, this theory does not apply to the DMB of BC patients during chemotherapy. Given that the ITHBC is a comprehensive health behavior change theory and provides clear elements that may relate to health behavior, we used the concepts and factors of this theory as the theoretical basis for the construction of the content of this intervention. The outcome stated in this theory was used as the outcome indicator of this intervention to verify the effect. In previous studies, the control group received standard health education from the department at admission. According to the ITHBC, the expected benefits of the intervention include better DMB and physiological and psychological health conditions.

This study is the first multidisciplinary early intervention during the beginning and middle of the chemotherapy cycle to improve DMB in BC patients, focusing mainly on health self-management behavior and lifestyle promotion based on the theoretical guidance of the ITHBC. This intervention may save large amounts of medical resources and significantly enhance patients’ confidence in their health management participation, which can help them maintain their nutritional status and prepare them for later recovery during the survival period. In addition, multidisciplinary interventions enable management by health professionals while simultaneously promoting patient self-management, ensuring continuous and comprehensive healthcare services. The aim of this randomized controlled trial (RCT) is to explore the feasibility of a multidisciplinary early dietary management intervention provided during chemotherapy from the perspective of health behavior change theory and its effectiveness on DMB (proximal outcome) and quality of life (distal outcome) in female BC patients.

## Methods/design

This manuscript followed the Standard Protocol Items: Recommendations for Interventional Trials (SPIRIT) guidelines [26] (Supplementary materials 1). Ethics approval was granted by the ethics committee of the Second Affiliated Hospital of the Fourth Military Medical University (number: K202305-41). This trial was registered with the Chinese Clinical Trials Registry (ChiCTR2300076503; October 10, 2023).

### Study design

A prospective 8-week, two-arm, single-center, single-blinded parallel-group RCT with a pretest and follow-up will be conducted by an MDT. Female patients who are diagnosed with BC and waiting to start chemotherapy or who are in the early or middle stage of chemotherapy will be randomized to receive either usual dietary care or the multidisciplinary early dietary management intervention. The participants in the intervention group will receive the multidisciplinary early intervention measures constructed based on the ITHBC. In contrast, the control group will receive only the usual cancer dietary care education at admission and education manuals based on the Dietary Guidelines for Chinese Residents, the World or American Guidelines, etc. The intervention consists of the following eight themes, with sessions provide once per week: adverse reaction coping, dietary information and habit regulation, self-care self-efficacy training, treatment self-regulation training, dietary supplement and TCM use, social support seeking, weight management, and outcome expectation education. Detailed information is provided in Fig. 1. Eight intervention sessions will be provided throughout admission for chemotherapy and a home-based interval chemotherapy period. This intervention will be initiated during the early and middle stages of chemotherapy. Standard chemotherapy cycles include 4, 6, and 8 cycles. For example, for patients receiving 4 chemotherapy cycles, the first intervention session will be provided during the first or second admission for chemotherapy. For patients receiving 6 cycles, the first intervention session will be provided during the first, second, third, or fourth admission. For patients receiving 8 cycles, the first intervention session will be provided during the first, second, third, fourth, fifth or sixth admission. The duration of intervention sessions during different chemotherapy cycles is shown in Fig. 2. In addition to the baseline measurements, follow-up measurements were taken immediately after the end of the intervention (T_1_) and at 1 (T_2_), 3 (T_3_), 6 (T_4_) and 12 months (T_5_) after the intervention. T_1_ was measured immediately after the end of the eighth intervention session. T_2_, T_3_, T_4_ and T_5_ will be measured 30, 90, 180 and 360 days after the T_1_ measurement date, respectively. The intervention process is shown in Fig. 3. The same time points for follow-up in the intervention group will be also used for the control group.

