Intervention session 1 (topic: adverse reaction management): After the participants receive chemotherapy during admission and 1 day before hospital discharge, the MDT members will introduce themselves and the describe intervention process face-to-face, and patients will become familiar with each other. This session will include group interventions, group discussions and lectures: (1) patients will share their experiences with chemotherapy and diet; the group will discuss their own disease and chemotherapy experiences and diet change trajectory; (2) a nurse will show a professional video from the China Central Television (CCTV) “Health Road” program about BC, chemotherapy and diet; (3) oncologists, nurses, and dietitians will introduce the trend of common adverse reactions and the corresponding dietary self-management tips during different chemotherapy periods, including early, middle, and late-term chemotherapy or chemotherapy during admission or the interval period; and (4) oncologists will clarify the boundaries between dietary self-management and medication management when adverse reactions occur.Intervention session 2 (topic: dietary information and habit regulation): A combination of online group and individual intervention sessions will be conducted during the first week of the home-based interval chemotherapy period after session 1, which will include the following: (1) oncologists and dietitians will hold an online group Tencent conference to introduce authoritative sources of dietary information for cancer patients, such as WeChat public accounts, short videos, guidelines, and distributed information in the form of electronic materials; (2) dietitians and TCM practitioners will focus on correct dietary habits and misunderstandings for individuals with different demographic characteristics during telephone calls or WeChat messaging, including discussing the relationship between dietary intake and hormone levels for hormone receptor-positive patients, providing nutrition and weight management clinics and food therapy for patients with higher family income or abnormal weight; and (3) dietitians will demonstrate methods of dietary intake self-assessment by online video presentations, using simple and intuitive representations such as “a handful, a fist, 1 g or 2 g of quantitative salt spoons”.Intervention session 3 (topic: self-care self-efficacy training): The online group session during the second week of interval chemotherapy after session 1 will include the following: (1) nurses will guide patients to disclose their concerns about participating in their diet self-management; (2) the psychologist will lead “evidence check” and “advocate” sessions: patients will be asked to write evidence for and against their participation in dietary self-management on two post-it notes and then play the advocate, attacking the evidence against participation; and (3) nurses will provide diet option comparison cards to show patients the pros and cons of different dietary habits and encourage all patients to choose and share the reasons.Intervention session 4 (topic: treatment self-regulation training): Online group and individual sessions will be conducted during the third week of interval chemotherapy after session 1, which will include the following: (1) Through WeChat, the psychologist will send patients an assessment questionnaire linked to treatment self-regulation. According to the results, the patients will be divided into four groups: the autonomous motivation, introjected regulation, external regulation, and amotivation groups [31]. Then, the psychologist will explain definitions, content, and performance to the same online group Tencent conference; (2) the psychologist will explain the relationship between mood and diet and then use “identifying automatic thoughts” and “testing hypotheses” to determine the cognitive reasons for the lack of motivation among patients in the amotivation group in the process of participating in diet self-management and demonstrate stress relief techniques, such as deep breathing and listening to soothing music; and (3) nurses will invite patients in the autonomous motivation and introjected regulation groups to share their diet self-management experiences and the goals achieved.Intervention session 5 (topic: dietary supplement and TCM use): The next admission chemotherapy period after the session, which will include a face-to-face group lecture and discussion one day before hospital discharge, will include the following steps: (1) dietitians and TCM practitioners will use videos, charts, and paper materials to explain the concept, indications, and types of dietary nutritional supplements and replacement therapy (which can be divided into two categories: edible nutritional supplements as well as complementary and alternative therapies, such as moxibustion, massage, and aromatherapy); (2) through clinical practice and scenario simulations, using pictures or natural objects, oncologists and dietitians will guide patients in analyzing and choosing dietary supplements and replacement therapies according to their conditions; and (3) TCM practitioners will describe the content of food therapy that Chinese patients are interested in, popularize scientific knowledge and correct misunderstandings.Intervention session 6 (topic: social support seeking): Online group and individual sessions will be performed during the first week of home-based interval chemotherapy after session 5, which will include the following: (1) warm small things to share and express gratitude: nurses will encourage patients to write down the names of people who prepare their meals and living arrangements during chemotherapy through an online group Tencent conference and prepare a sentence, video or gift for them. (2) The psychologist will provide targeted dietary management tips related to emotion and psychology depending on the working status of patients via WeChat or telephone. For employed females, dietary advice will be provided to their families or colleagues before they return to work. Nonemployed individuals will be encouraged to share their thoughts and preferences regarding their diet with friends or neighbors who would like to help take care of them. (3) Nurses will encourage patients to share how others can help improve their diet during chemotherapy and how they seek help.Intervention session 7 (topic: weight management): Online group and individual sessions will be provided during the second week of the interval chemotherapy period after session 5, which includes (1) oncologists informing patients that being overweight is a risk factor and showing patients how to correctly measure their body weight via an online video, calculate their body mass index (BMI) and determine their BMI classification. (2) Dietitians will introduce the criteria and ranges of daily caloric intake for patients with different BMI classification via WeChat or telephone. For example, overweight and obese patients will be taught to read ingredient lists and recipes. Patients with a BMI below the normal range will be taught to choose foods rich in high-quality fat (such as omega 3 fatty acids and monounsaturated fatty acids) and protein [29, 30]. Repeated operations and repetitions will be used to test the effect. (3) Nurses will show patients and their caregivers how to exercise moderately and record daily calories using apps or memos.Intervention session 8 (topic: outcome expectation education): An online group session during the third week of interval chemotherapy after session 5 will include the following: (1) the psychologist will introduce the concept, content, necessity, classification and function of the outcome expectation related to dietary self-management to patients by an online group Tencent conference; (2) Nurses will encourage patients to write down their expectations for diet self-management on post-it notes and classify them into immediate or future goals; (3) The psychologist will use the “five-column chart” of alternative thinking to ask patients to share their views on the outcome expectations and determine the negative cognition of achieving the goal; (4) Through scenario and case studies, the psychologist will lead patients to analyze their own cognition on two outcome expectations of what points may be right or wrong, encourage them to create new goals and teach them how to stick to long-term dietary self-management monitoring; and (5) MDT members will summarize and share the gains and suggestions of this intervention with patients.

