### Other outcomes

#### Demographic and clinical information

Self-designed demographic and clinical factor questionnaires will be used to collect this information. To ensure the representativeness and comprehensiveness of the demographic and clinical factors of BC patients as much as possible, we referred to guidelines and previous literature related to diet, nutrition, lifestyle, and self-health management in BC patients treated with chemotherapy. After discussion among the research team members, the questionnaire will be used to collect demographic (age, BMI, marital status, number of children, educational level, per capita monthly household income, living conditions, work status, and menopausal status) and clinical information (time of diagnosis, unilateral or bilateral BC status, cancer stage and chemotherapy type).

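### The early intervention may start after anything from 12.5% to 75% of planned chemotherapy, and start position has no listed place in the data, the allocation or the analysis model

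*Protocol article*

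**What the plan says.** The Study design section sets the start window by regimen. The shortest: "for patients receiving 4 chemotherapy cycles, the first intervention session will be provided during the first or second admission for chemotherapy". The middle: "For patients receiving 6 cycles, the first intervention session will be provided during the first, second, third, or fourth admission". The longest: "For patients receiving 8 cycles, the first intervention session will be provided during the first, second, third, fourth, fifth or sixth admission". It labels the whole window: "This intervention will be initiated during the early and middle stages of chemotherapy".

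The section on implementation places session 1 late in the admission: "After the participants receive chemotherapy during admission and 1 day before hospital discharge". Sessions 2 to 4 fall in the three following weeks at home, session 5 at the next admission, and sessions 6 to 8 in the three weeks after that. T1 is taken at the end of session 8. T2 to T5 follow 30, 90, 180 and 360 days later, and controls use the same time points.

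The case for acting early is put in the Abstract: "Adverse reactions are prone to occur in the early stage of chemotherapy and can negatively affect the dietary intake and nutritional status". The Background states the aim, which is to "explore the feasibility of a multidisciplinary early dietary management intervention provided during chemotherapy" and to assess its effect on dietary management behaviour and quality of life.

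The clinical items to be collected are listed as "clinical information (time of diagnosis, unilateral or bilateral BC status, cancer stage and chemotherapy type". The Randomization section describes 1:1 allocation of 88 patients from a random number table and states no stratification. The Statistical analysis section names time, group and interaction effects.

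**The concern.** The trial is justified by dietary disruption that begins early in chemotherapy, yet its window admits patients for whom most of the chemotherapy is over. Visits are counted from session 8, so a given visit finds some patients in mid-treatment and others finished. One of the four DMBQ domains is coping with adverse reactions, so the phase of treatment may plausibly act on the primary score directly. That would make start position a prognostic variable and possibly an effect modifier.

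Two things are at stake. First, a variable that could explain part of the outcome variance is left out of the stated model. Second, the title and discussion speak of early intervention, while the estimate will be an average over early and fairly late starts in unknown proportions. A reader could not tell to whom it applies.

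**Working it through.** The article gives no figure for the share of chemotherapy received at the start, so there is none to reproduce. The inputs are the start windows and session timing above, and 44 patients per arm (Sample size section).

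**1. Chemotherapy given by session 1.** Let N be planned cycles and k the admission at which session 1 is held. Session 1 follows that admission's chemotherapy, so the fraction given is k/N.

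**2. Cycles left at T1.** Session 5 is at admission k+1 and session 8 falls in the interval after it, so N − (k+1) cycles remain.

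| Planned cycles | Earliest start: given | Latest start: given | Left at T1, earliest start | Left at T1, latest start |
|---|---|---|---|---|
| 4 | 1/4 = 25% | 2/4 = 50% | 4 − 2 = 2 | 4 − 3 = 1 |
| 6 | 1/6 = 16.7% | 4/6 = 66.7% | 6 − 2 = 4 | 6 − 5 = 1 |
| 8 | 1/8 = 12.5% | 6/8 = 75% | 8 − 2 = 6 | 8 − 7 = 1 |

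Counting only cycles completed before the starting admission, (k−1)/N, the latest starts are 25%, 50% and 62.5%.

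**3. What a visit means.** Assume that the four-week spacing implied by the session schedule continues. T1 is then 7 weeks after session 1, and the last cycle falls 4(N−k) − 7 weeks after T1. For a start at 6 of 8 this is 4×2 − 7 = 1 week. For a start at 1 of 8 it is 4×7 − 7 = 21 weeks. At T3 (90 days, about 12.9 weeks) the first patient is about 12 weeks past the last cycle. The second has cycles at weeks 13, 17 and 21 still to come.

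**4. Chance imbalance.** Assume for illustration that all patients have 8 cycles and starts are spread evenly over admissions 1 to 6. The SD of remaining cycles is √((6² − 1)/12) = 1.71. The standard error of the arm difference is 1.71 × √(2/44) = 0.36, and 1.96 × 0.36 ≈ 0.7 cycle marks the edge of the 95% range. In terms of late starters, with 88 patients split 44/44 without stratification, the chance of an imbalance of 15 percentage points or more (hypergeometric) is about 6%, 10% or 13.5% if 20%, 30% or 50% of patients start late. These shares are assumed.

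**5. Could the trial show that timing matters?** Take an outcome with SD 1, an even early/late split and no loss. The standard error of the arm-by-timing term is 4/√88 = 0.426. By normal approximation, power is Φ(d/0.426 − 1.96):

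- d = 0.5 SD: 22%
- d = 0.8 SD: 47%
- d = 1.0 SD: 65%

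With 72 patients (SE 4/√72 = 0.471) the figures are 18%, 40% and 56%.

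**6. Entry rules side by side.** Study design randomises women waiting to start chemotherapy and women already in its early or middle stage. The Abstract's Methods and inclusion criterion 4 require that this stage has not yet begun. Read strictly, criterion 4 would exclude the late starters on whom the 75% rests.

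**The case against.** A reader might infer that the trial cannot answer its own question. The documents do not support that. The stated aim is a comparison with usual care, with no early-versus-late objective, and the window is openly declared as early and middle. 'Early' is also set against previous studies in survivors who had completed all adjuvant therapy. The latest start has a logic too: beginning at admission N−2 puts session 8 before the last cycle, so the whole programme falls within chemotherapy.

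A reader might also infer bias. Both arms are drawn from the same window by randomisation, so start position brings chance imbalance and extra variance but no systematic error, and the test's error rate already allows for chance imbalance. No figure in the article links remaining cycles to DMBQ points, so the effect on the scores cannot be sized.

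A third inference, that the variable is not recorded and correction is impossible, is unproven. Criterion 4 cannot be applied without knowing planned cycles and current admission, criterion 2 requires an established order and regimen, and a full protocol or analysis plan may hold both items.

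All of this stands. What it leaves is narrower. The article does set out its clinical items and its model effects, and start position is in neither, although the value is in hand at screening.

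**Conclusion.** The point holds as a worthwhile improvement and a limit on interpretation; it does not invalidate the comparison. The range of 12.5% to 75% and the 1 to 6 cycles left at T1 follow directly from the stated schedule, given the Study design reading of who may enter. The visit dates in step 3 and the imbalance figures rest on the assumptions shown there.

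The average effect over the enrolled mix can be estimated. Without the covariate, whatever precision start position could add is forgone: in a simple linear model the residual variance would fall by a factor 1 − r², where r is its correlation with the outcome, which the article does not give. Nor can a positive result be attributed to early starting, or a null result to late starting. Adding an interaction term would not settle that, since power is only 22% to 65% for differences of 0.5 to 1.0 SD.

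**What to change.** 1. Retain two baseline items from the chemotherapy order at enrolment: planned number of cycles and admission number.
2. Include the fraction of planned chemotherapy given at enrolment as a covariate in the primary model, whether repeated-measures ANOVA or GEE. Fix it before randomisation and define it identically in both arms. The fraction at session 1 should not be used, because it arises after allocation and controls have no session 1. For a patient enrolled just before admission k, the value is (k−1)/N, from 0 to 5/8 = 62.5%.
3. Show the distribution of this fraction by arm.
4. Word conclusions as applying to starts across the early-to-middle window.
5. Label any arm-by-fraction estimate exploratory.
6. Reconcile the Study design section with the Abstract's Methods and criterion 4 on whether women already in the early or middle stage may enter. If nobody may have begun chemotherapy at enrolment, the fraction is zero for all and only planned cycles would remain to adjust for.

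The cost is two fields already needed for screening, one degree of freedom and a few sentences. The start window need not change.
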